### 2.6. Screening and Self-Administered Questionnaire

Participants will complete a QR code online application form soliciting sociodemographic information (age, gender, educational background, marital status, monthly household income, living circumstances, employment status, psychiatric history and duration of having anxiety symptoms (in years/months), currently taking prescribed or over the counter anxiolytics (yes/no), family history of anxiety disorder (yes/no) and other psychiatric disorders, etc.) before filling in the screening tool (Insomnia Severity Index).

### 2.7. Randomization, Allocation and Masking

All consenting participants will be listed in alphabetical order according to their surnames and each participant will be assigned a unique identifier. An independent statistician will use a computer-generated list of random numbers (www.random.org, accessed on 1 June 2022) to ensure concealment of randomization. Randomization will be conducted by an independent statistician off-site using a stochastic minimization programme to balance gender, age, and ISI scores of the participants. Block randomization with blocks of 10 (total: 6 blocks) will be used to allocate treatment groups. Participants from each block will be randomly assigned to the active VeNS groups or the sham VeNS group on a 1:1 ratio. To avoid information flow, participants and research associates will be blinded to the group allocation to minimize potential contamination of the effects of VeNS or subject bias. The principal investigator will not be involved in data collection or pre-and-post VeNS measurements. Outcome measurements will be conducted by research associates who are not involved in the group allocation. Participants will be asked to guess the grouping (active VeNS vs. sham VeNS) in the face-to-face follow-up meetings after finishing the 4-week interventions, to determine the success of subject blinding [36].

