## 2. Materials and Methods

### 2.1. Trial Design

This is a two-armed, double-blind, randomized, sham-controlled trial evaluating the effects of a 4-week VeNS treatment on insomnia among Hong Kong adults in the general population. The study strictly complies with the Consolidated Standards of Reporting Trials (CONSORT) statement [33] and will be conducted in accordance with the Declaration of Helsinki [34] and Good Clinical Practice. Participants will be randomized into the active VeNS or sham VeNS group on a 1:1 ratio, balanced by their Insomnia Severity Index score, gender, and age. All the participants will be fully informed about the randomization procedures and that they have a 50% chance of receiving the active VeNS or the sham VeNS in this trial. Both groups will be measured at four time points: baseline (T1), immediately after the 4-week intervention (T2), at 1-month (T3), and 3-month follow-up (T4) (Figure 1).

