##### Quality of Life

Quality of life will be assessed by the Chinese version of the 36-item Short Form Health Survey (SF-36) [42]. The SF-36 includes 36 questions related to an individual’s QoL on eight scales: physical functioning (PF), role—physical (RP), bodily pain (BP), general health perceptions (GH), vitality (VT), social functioning (SF), role—emotional (RE), and mental health (MH). The raw scores for each scale are transformed to a scale of 0–100, with higher scores indicating ‘better’ QoL. SF-36 is summarized in two component summary scores: the Physical Component Summary (PCS) and the Mental Component Summary (MCS). This Chinese version of SF-36 is a valid and reliable instrument, with the overall Cronbach’s α coefficient of 0.943, while the Cronbach’s α coefficients for each of the dimensions found to be all >0.70 [43].

All the primary and secondary outcomes will be assessed at baseline, at 4-week posttreatment, 1-month, and 3-month posttreatment for immediate, and short-term effects [44].

**Trial Status:** This trial was registered with ClinicalTrials.gov on 9 August 2022 (protocol version) (identifier: NCT04452981). Recruitment commenced between 1 June 2022 and 30 December 2022.

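### Section 2.7 states two allocation rules, minimisation and unstratified blocks of 10, without saying which governs; if the blocks do, the balance promised in section 2.1 is not provided by design

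*Protocol article*

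**What the plan says.** Section 2.7 of the protocol article describes allocation in five steps:

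- A roster: "All consenting participants will be listed in alphabetical order according to their surnames and each participant will be assigned a unique identifier".
- A source of random numbers: "An independent statistician will use a computer-generated list of random numbers".
- A covariate-adaptive rule, run off-site by an independent statistician "using a stochastic minimization programme to balance gender, age, and ISI scores of the participants".
- A blocked rule: "Block randomization with blocks of 10 (total: 6 blocks) will be used to allocate treatment groups".
- The assignment within blocks: "Participants from each block will be randomly assigned to the active VeNS groups or the sham VeNS group on a 1:1 ratio".

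Section 2.1 describes the result as 1:1 groups "balanced by their Insomnia Severity Index score, gender, and age". Section 2.5 sets 30 subjects per group, 60 in all. Section 3 fits a mixed model with group, time and their interaction. It brings in covariates only if the sociodemographic comparison between groups turns out significant. The Trial Status note at the end of section 2.12.2 gives the recruitment window: "Recruitment commenced between 1 June 2022 and 30 December 2022".

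**The concern.** Minimisation and blocking are different answers to the same question. Under minimisation, the next assignment depends on the gender, age and ISI of those already allocated. Under blocks of ten with random 1:1 assignment inside each block, five go to each arm whatever their covariates. The article gives both in consecutive sentences, with no order of precedence, no strata for the blocks and no combining rule.

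Two things depend on which rule was meant. The first is the promise in section 2.1: minimisation supports it, unstratified blocks do not. The second is the analysis. Factors used to steer allocation normally belong in the model, whereas section 3 makes covariates conditional on a significance test of sociodemographic differences. A reader cannot judge whether that model matches the design without knowing the design.

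An article may leave cut-points and the biased-coin probability to a fuller document. Here, however, the text itself states two rules that do not fit together.

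**Working it through.** **Step 1: the plan's own figure.** 6 blocks × 10 = 60, which equals 2 × 30 from section 2.5. The block count is consistent, so the arithmetic is not the problem.

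**Step 2: the two rules side by side.**

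| | Minimisation | Blocks of 10 |
|---|---|---|
| What decides an assignment | covariates of those already allocated, plus a random element | random order within the block |
| Gender, age, ISI used | yes | no (no strata named) |
| 5:5 in each ten | not guaranteed | guaranteed |
| Section 2.1 balance by design | yes | no |

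**Step 3: chance imbalance under unstratified blocks.** Input: 30 per arm (section 2.5).

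- SD of the difference in baseline means = SD × √(2/30) = 0.258 SD.
- P(|difference| > 0.25 SD) = 2 × [1 − Φ(0.25/0.258)] = 2 × [1 − Φ(0.968)] = 0.33.

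**Step 4: simulation of the alternatives.** Each scheme was run on 3,000 simulated trials of 60. These inputs are assumptions, not in the article: probability 0.8 for the arm that reduces imbalance; age uniform on 18–60, split at 39; ISI uniform on 16–23, split at 20; one gender making up 50% or 70%. The age threshold of 0.25 SD is 0.25 × 42/√12 = 3.03 years. The hybrid is minimisation overridden once an arm has five in the current ten. Ranges cover the two gender mixes.

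| Scheme | Gender gap ≥ 20 points | ISI gap ≥ 0.25 SD | Age gap ≥ 0.25 SD | Not 30:30 | 5:5 in all six tens |
|---|---|---|---|---|---|
| Simple randomisation | 9.4–12.2% | 32.2–34.0% | 34.4–35.7% | about 90% | about 0% |
| Unstratified blocks of 10 | 12.0–16.1% | 32.8–33.3% | 33.5–34.0% | 0% | 100% |
| Minimisation | 0.2–0.3% | 9.4–9.5% | 10.1–10.2% | 46.5–46.9% | 3.5–4.0% |
| Hybrid | 0.3–0.7% | 10.9–11.7% | 11.1–11.4% | 0% | 100% |

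**Step 5: reading the results.** The simulated ISI figure for blocks agrees with step 3. Blocks equalise the group sizes but do nothing for the three covariates. Minimisation left to itself gives six 5:5 blocks in only about 4% of trials, so it would rarely look like the block scheme by accident. A rule combining the two is feasible and keeps nearly all of the balance, but the article does not describe one.

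**The case against.** The strongest reply is that the methods can coexist. The blocks may be batches of ten participants, with the off-site programme balancing covariates inside each batch. The article does not use the word permuted or say that the sequence is fixed in advance. The hybrid in the working shows that such a scheme works. This stands as far as it goes: what is missing is the combining rule, and it would be wrong to say that minimisation and blocks can never be used together. But the text says that participants within a block are assigned at random 1:1, mentions no covariate there, and gives no rule linking the two.

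Three stronger readings are tempting, and the article does not support them:

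- **That every listed element conflicts.** A reader might count the random-number list and the roster as further incompatible mechanisms. They are not in themselves. The list could generate the block order or supply the random element of minimisation.
- **That the roster requires everyone to consent before the first allocation.** An alphabetical list of all consenting participants sits awkwardly with a window from June to December 2022. However, the article does not say that there is one closed list, and batch-wise listing would fit. The recruitment sentence is loosely worded and says nothing about when allocation takes place. The roster needs clarifying; it is not a proven contradiction.
- **That the trial is biased, or that a baseline gap of about 0.25 SD removes nearly a third of the d = 0.8 sought.** Either method alone is valid randomisation. The imbalance has expectation zero and is ordinary chance variation at 30 per arm. T1 is also a time point in the mixed model, so a raw baseline ISI gap does not pass one-for-one into the group × time effect.

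**Conclusion.** Section 2.7 contradicts itself on a stated design rule: minimisation and unstratified blocks are each said to determine allocation, and as written both cannot. If the blocks govern, the balance on ISI, gender and age claimed in section 2.1 is not secured by design. The chance of a baseline ISI gap above 0.25 SD is then about one in three rather than roughly one in ten.

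The one-in-three figure needs only 30 per arm and approximate normality of the mean difference. The one-in-ten figure rests on the assumed 0.8 coin and two-level age and ISI factors, and would shift with other choices. The harm is an unidentifiable mechanism and an unsupported balance claim. Concealment, type I error and validity of the randomisation are not shown to be at risk.

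**What to change.** Name one governing method in section 2.7 and align sections 2.1 and 3 with it.

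- **To keep the promise in section 2.1:** state that allocation is by stochastic minimisation on ISI, gender and age, giving the random element (0.8 is only an example). Alternatively, describe a hybrid held to 5:5 within batches of ten. Include the three factors in the mixed model of section 3 regardless of any baseline significance test. Gender and age enter as covariates. State how baseline ISI enters, either as a covariate with T2–T4 as responses or through T1 as a response, so that it is not used twice.
- **If unstratified blocks were actually used:** say so, and delete the minimisation statement in section 2.7 and the balance claim in section 2.1.
- **In either case:** the random-number list may stay if its role is stated. Reconcile the alphabetical roster with allocation during ongoing recruitment, for example by saying whether allocation is in batches.

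The cost is a text change, a matching line in the model specification, and confirmation from the independent statistician of what was run. No extra participants or staff are needed.

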### 2.8. Interventions

In this study, all participants (in both active and sham VeNS group) will collect a VeNS device for home use in our Integrative Health Clinic, SN, PolyU, after the device training delivered by the research associates. Participants will receive 20 VeNS sessions in this study, with each session lasting for 30-min over a 4-week period (i.e., Monday–Friday, total treatment time: 10 h). We believe that a four-week VeNS intervention will be sufficient enough to test the efficacy of VeNS on insomnia [35]. Participants will be followed up immediately after post-stimulation at 4 weeks and 12 weeks (Figure 1, CONSORT Flow Diagram). We believe that a post-stimulation follow-up of up to 3 months is sufficient to evaluate the sustainability of VeNS.

#### 2.8.1. VeNS group

Subjects should download the study app (Vestal) prior to each VeNS stimulation session. Subjects will put on the VeNS headset, and apply two self-adhesive electrode pads on the mastoid process behind the ear. Subjects should remain in a sitting down and resting position throughout the stimulation period. Subjects should place the electrodes on both mastoid processes simultaneously in each treatment session. Subjects will then turn on the device which will then deliver a small electrical impulse (range from 0 mA to max. 1 mA, level 0–10) at 100 Hz. Subjects should initially feel a comfortable tingling sensation around the mastoid process and soon after they should feel a gentle swaying indicating modulation of the vestibular nerve and that will be the optimal level of stimulation for individual participant. After selecting the stimulation level, the VeNS device will then deliver the stimulation for 30 min when participants press the ‘start’ button, and the device will automatically turn off. Subjects will then remain with that level until the stimulation is over.

Subjects will be able to check their activities on the study app and modify the stimulation level via the study app. The device can be paused/stopped by pressing the power button via the study app. Subjects will hear a single beep sound whenever they change the stimulation level. After the stimulation, subjects can remove the headset and dispose the electrode pads.

#### 2.8.2. Sham VeNS

Subjects in the sham-controlled group will follow the identical procedures as set in the VeNS group. Subjects will receive the initial stimulation for 30 s and then tap down to 0 mA for 20 s. Subjects in the sham-controlled group will receive a sham VeNS stimulation at a frequency of 0.8 Hz due to the fact that this frequency has a low sympathetic activation, and is less likely to cause any improvement in the sham-controlled group. An older study [37] also mentioned that sinusoidal galvanic vestibular stimulation (GVS) delivered at 0.5–0.8 Hz can cause partial entrainment of muscle sympathetic nerve activity (MSNA), and thus, we will use 0.8 Hz for the sham-controlled group in this trial. Subjects will also experience sensation of skin tingling and vestibular stimulation so that subjects in this group will believe that they have been allocated with an active device.

On completion of each VeNS session, subjects will charge the device using the micro-USB and charger provided by the project team, for usage in the next stimulation session. The device will automatically stop the stimulation after 30 min usage per day and subjects will need a 16 h lock-out period to re-use the device again. All participants will be reminded that any form of sleep tracker is prohibited in this trial.

Data will be collected via the Bluetooth for the device. The total usage per day, average intensity used, and average resistance will be logged and stored on an encrypted server. The study app will upload these data automatically when connected to Wi-Fi. All individual data with a unique trial identifier allocated at the recruitment time will be collected via REDCAP by the PI and recorded in the electronic case report form (CRF).

### 2.9. Fidelity

To ensure the fidelity of the intervention, the project team will ascertain whether the interventions will be delivered as designed. To ensure compliance, the project team will monitor the duration of usage data on a weekly basis (Friday). If any subject’s weekly usage is <2.5 h, the research associates will send a WhatsApp text message as a gentle reminder and investigate if subject experiences any technical issues in using the device. The PI will work closely with the research personnel to optimize compliance throughout the study period.

### 2.10. Safety, Adverse Effects and Risk Indicators

Past research [38] was conducted on skin inspection of the mastoid area, otoscope examination of the inner ear, and formal audiometry testing on 25 VeNS long-term daily or regular users (2–3 times/week) examining the safety of the MS device. Results showed that these long-term NeVS users had a mean duration of VeNS use for 22 months and they did not show any abnormality through examination of the mastoid areas, ear canal, or tympanic membranes nor audiogram assessments. In this regard, VeNS is safe and well tolerated by Modius Sleep users.

However, some subjects may have skin irritation at the electrodes’ sites, sensation of disequilibrium, nausea/vomiting, headache, and an electrical tingling sensation. Hence, an adverse events checklist will be used to monitor/quantify the occurrence of these events between the VeNS group and the sham VeNS group. Subjects are encouraged to contact the project team members should these adverse effects become too unmanageable. The PI will then assess the subjects’ physical and mental conditions and decide whether they could continue the intervention or not.

### 2.11. Ethical and Data Security Considerations

Ethical approval will be obtained from the Human Subjects Ethics Sub-committee, Hong Kong Polytechnic University. This study adheres strictly to the Declaration of Helsinki ethical principles developed by the World Medical Association. All participants will be covered by trial insurance. Potential risks involved in NeVS will be clearly indicated in the Information Sheet. Voluntary participation, anonymity and confidentiality and the right to withdraw will be respected.

Participants’ data in both groups will be stored in two separate datasets with an identifier linking these data. Both sets of data will be encrypted using TrueCrypt (http://www.truecrypt.org). The data from baseline, and the four-week, one-month and three-month follow-up will be linked according to personal data. All precautions in data protection will be taken, as suggested by TrueCrypt. To prevent leakage of personal data, only the PI will have access to the personal dataset. Written consent will be obtained from all participants. An information sheet containing the purpose of this trial and the VeNS procedures and the Modius Stress leaflet will be provided to all participants. Participants will be informed of their anonymity; withdrawal or non-compliance will not result in any consequences.

### 2.12. Outcome Evaluation (Primary and Secondary Outcomes)

The primary objective of this study is to evaluate the effects of VeNS on participants’ insomnia severity among adults in Hong Kong. Secondary objectives include examining the effects of VeNS data usage on insomnia severity, sleep quality, and quality of life.

#### 2.12.1. Primary Outcome

##### Insomnia Severity

Insomnia severity will be assessed by the Chinese version of the Insomnia Severity Index (ISI) which consists of 7 items measuring day and night symptoms of insomnia on individuals. This ISI consists of seven items (1: perceived difficulty, 2: falling asleep; 3: time of awakening; 4: satisfaction with current sleep pattern; 5: interference with daily functioning; 6: noticeability of others of impact of lack of sleep; 7: degree of perceived distress/concern caused by the sleep problem). Subjects will rate each question on a 5-point Likert scale (0–4), with score ranges of 0–28, with 15–21 indicating moderately severe insomnia. ISI has been used in the Chinese population with good psychometric properties, with Cronbach’s alpha 0.81 and item-to-total correlations in the range of 0.34–0.67 [39].

#### 2.12.2. Secondary Outcomes

##### Sleep Quality

The Pittsburgh Sleep Quality Index (PSQI) [40] will be used to assess sleep quality over the past month. The PSQI consists of 19 items in total. Participants type in their responses to the first 5 questions asking about their bedtime, time taken to fall asleep, wake up time, actual sleep time, and time in bed in the past month. Next, they respond to the remaining 14 questions that ask about the frequency of sleep problems, use of sleeping pills to go to sleep and daytime sleepiness on a Likert-type scale ranging from 0 to 3, with a higher value indicating more severe sleep problem. A score of ≥5 indicates poor sleep quality. Total score ranges are 0–21. If total score increases, it indicates a decrease in sleep quality. The Chinese version of the PSQI is a reliable and valid instrument to assess sleep quality among the Hong Kong Chinese population [41].

##### Quality of Life

Quality of life will be assessed by the Chinese version of the 36-item Short Form Health Survey (SF-36) [42]. The SF-36 includes 36 questions related to an individual’s QoL on eight scales: physical functioning (PF), role—physical (RP), bodily pain (BP), general health perceptions (GH), vitality (VT), social functioning (SF), role—emotional (RE), and mental health (MH). The raw scores for each scale are transformed to a scale of 0–100, with higher scores indicating ‘better’ QoL. SF-36 is summarized in two component summary scores: the Physical Component Summary (PCS) and the Mental Component Summary (MCS). This Chinese version of SF-36 is a valid and reliable instrument, with the overall Cronbach’s α coefficient of 0.943, while the Cronbach’s α coefficients for each of the dimensions found to be all >0.70 [43].

All the primary and secondary outcomes will be assessed at baseline, at 4-week posttreatment, 1-month, and 3-month posttreatment for immediate, and short-term effects [44].

**Trial Status:** This trial was registered with ClinicalTrials.gov on 9 August 2022 (protocol version) (identifier: NCT04452981). Recruitment commenced between 1 June 2022 and 30 December 2022.

## 3. Statistical Analyses

All statistical analyses will be performed by R for Windows (R version 4.1.0). Normal distribution of the data will be assessed by a Q-Q plot. Descriptive analysis that include means and standard deviations (SD) for the continuous variables will be presented, while numbers and percentages for the categorical variables will also be shown. A *p* value < 0.05 is considered statistically significant. Sociodemographic differences between the active VeNS group and the sham VeNS group will be analyzed using Chi-square test and *t* test. Should there be significant differences in sociodemographic factors between the two groups, covariates will be considered as confounding variables in the statistical analyses. Normality of the primary outcome (ISI) scores will be tested by the Shapiro–Wilk test. The independent samples *t* test will be used to test the baseline difference between the two groups.

A mixed model will be used to test the group (between-subject factor), time (within-subject factor), and group × time interaction effects of the ISI score between the active VeNS group and the sham VeNS group. Post hoc comparisons between groups and time points will be conducted using a *t* test with Bonferroni correction. A Cohen’s *d* effect size for each outcome will be calculated, where *d* = 0.2, 0.5, and 0.8 correspond to small, medium, and large effect size. Participants’ total usage time will also be used to investigate the effectiveness of the VeNS on anxiety and total usage time will be used as a continuous covariate in a linear regression model for ISI total score. Missing data will be managed by multiple imputation [45] by adopting the last observation carried forward (LOCF) method.

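### Covariates are chosen by baseline significance tests, while no adjustment is named for ISI, age and gender, the factors used to balance allocation

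*Protocol article*

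**What the plan says.** Three statements in the protocol article bear on this point.

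- **Covariate rule (Section 3).** Arms are compared at baseline: "Sociodemographic differences between the active VeNS group and the sham VeNS group will be analyzed using Chi-square test and *t* test". The result decides adjustment: "Should there be significant differences in sociodemographic factors between the two groups, covariates will be considered as confounding variables in the statistical analyses". The general threshold applies: "A *p* value < 0.05 is considered statistically significant". After the sentence on normality of the ISI scores, the section adds: "The independent samples *t* test will be used to test the baseline difference between the two groups". No consequence is attached to that last test.
- **Primary model (Section 3).** "A mixed model will be used to test the group (between-subject factor), time (within-subject factor), and group × time interaction effects of the ISI score". No covariate is named.
- **Allocation (Sections 2.1 and 2.7).** The arms are to be "balanced by their Insomnia Severity Index score, gender, and age", by an independent statistician "using a stochastic minimization programme to balance gender, age, and ISI scores of the participants".

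Section 2.6 lists at least seven sociodemographic variables: age, gender, education, marital status, household income, living circumstances and employment.

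**The concern.** In a randomised trial, any baseline difference between arms arises by chance. A small p-value for it does not show that the variable predicts ISI, and a large one does not show that it can be ignored. The rule therefore selects covariates on the wrong criterion.

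It also works against the design. If minimisation does its job, age and gender will rarely differ significantly, so the factors judged important enough to balance on are the least likely to be adjusted for. A prognostic balancing factor left out of the model gives standard errors that are too large.

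The final model cannot be known until the data are seen, and the wording leaves open which covariates then enter. At stake are a fixed primary analysis and some precision on ISI in a trial of 60 people.

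**Working it through.** **Inputs from the article.** Threshold 0.05 (Section 3); seven sociodemographic variables (Section 2.6), two of which, age and gender, are balancing factors; d = 0.8, 30 per arm, 20% attrition at the 12-week follow-up (Section 2.5). Evaluable number at that follow-up: 30 × 0.8 = 24 per arm.

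**Assumptions.** The article gives no correlation r between baseline and later ISI, so r = 0.3, 0.5 and 0.7 are used. d is taken on the SD of the post-treatment score, tests are two-sided, and SDs are equal at baseline and follow-up.

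**1. Chance of a false trigger.** For k independent tests under correct randomisation, P(at least one significant) = 1 − 0.95^k.

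- Five variables not balanced: 1 − 0.95^5 = 0.226, about 23%.
- All seven: 1 − 0.95^7 = 0.302, about 30%.

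The five-variable figure fits the design if minimisation is used. The seven-variable figure is an upper value, because it lets age and gender trigger at the full 5% each.

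**2. Precision for baseline ISI.** The article gives no figure to reproduce here. If T1 is a level of time, the group × time contrast at a visit is a difference in change from baseline. In units of the post-score variance:

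- change-score contrast: 2(1 − r)
- baseline-adjusted contrast: 1 − r²
- ratio: (1 − r²) / [2(1 − r)] = (1 + r)/2

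The standardised effects are 0.8/√[2(1 − r)] and 0.8/√(1 − r²). Power from the noncentral t distribution:

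| r | Variance ratio | Effect, change | Effect, adjusted | Power at 24 per arm, change vs adjusted | Power at 30 per arm, change vs adjusted |
|---|---|---|---|---|---|
| 0.3 | 0.65 | 0.676 | 0.839 | 63% vs 81% | 73% vs 89% |
| 0.5 | 0.75 | 0.800 | 0.924 | 77% vs 88% | 86% vs 94% |
| 0.7 | 0.85 | 1.033 | 1.120 | 94% vs 97% | 98% vs 99% |

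The stated attrition belongs to the last visit, so the T2 number should lie between 24 and 30 per arm.

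**3. Behaviour of a significance-triggered rule.** A simulation used 25 per arm, one baseline covariate with correlation 0.3, 0.5 or 0.7 to the outcome, and 6,000 runs per setting.

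| Randomisation | Type I error of triggered rule (r = 0.3, 0.5, 0.7) | Power, triggered rule | Power, always adjusted |
|---|---|---|---|
| Simple | 0.049, 0.048, 0.034 | 80%, 81%, 81% | 82%, 89%, 97% |
| Closely matched on the covariate | 0.036, 0.029, 0.008 | 80%, 83%, 86% | 83%, 90%, 97% |

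Under close matching the baseline test was never significant, so the rule never adjusted. Matched pairs balance more tightly than minimisation would, so that row is an extreme case. Its direction is what matters: the test becomes conservative.

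**The case against.** The strongest objection is that the baseline ISI part rests on silence. The conditional rule covers sociodemographic factors only, and ISI is not one of them. A reader might infer that the plan excludes baseline ISI from adjustment, or fits T1 as an outcome with an unconstrained group effect. The article supports neither. It lists T1 among four measurement times and names group, time and their interaction. Whether T1 is an outcome, a covariate or a constrained baseline could be settled in an analysis plan not shown here. This stands, and the power comparison is therefore conditional on T1 being a level of time.

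It does not rescue the covariate rule, which the article states outright and which is poor as written.

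Further points stand in part:

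- The gain shrinks as r rises. At r = 0.7 it is 94% vs 97% with 24 per arm. If d = 0.8 was meant on the change-score SD, the change contrast does not lose power as tabulated.
- Nothing in the article shows that age or gender predicts ISI, so the gain from those two is unquantified and may be small.
- Section 2.7 describes blocks of 10 as well as minimisation. Blocking alone would not balance age, gender or ISI. Those factors could then trigger the rule, and the 30% figure would be the relevant one.
- The tests are probably correlated (income, education and employment, for example), so 23% and 30% are approximate.

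**Conclusion.** The concern holds as a badly fixed rule that should be changed. Covariates enter by chance, with a false-trigger probability of about 23% (five variables) to 30% (seven), assuming independence. No adjustment is named for the three balancing factors.

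If T1 is a level of time, the loss against baseline adjustment is a variance factor of (1 + r)/2. At d = 0.8 the cost in power runs from about 18 percentage points (r = 0.3, 24 per arm) to about 1 (r = 0.7, 30 per arm). These figures rest on assumed r, a two-sided 0.05 test and d on the post-score SD.

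A reader might infer that choosing covariates after looking at baseline inflates the type I error. The calculations do not support that: it was 0.034 to 0.049 in the simulation with simple randomisation, and lower with close balance. The harm is data-dependence and lost precision. The planned analysis is not invalid.

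**What to change.** In Section 3, remove the baseline significance tests as a trigger for covariates and present baseline data descriptively. Before unblinding, pre-specify one of the following:

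- a mixed model for ISI at T2, T3 and T4 with arm, visit, arm × visit, baseline ISI (optionally by visit), age and gender; or
- a longitudinal model with T1 to T4 as outcomes, the arm means constrained equal at T1, and age and gender as covariates.

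State which is primary.

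The cost is wording. In the first model, baseline ISI, age and gender take 3 degrees of freedom, and letting the baseline slope differ across three visits adds 2, giving 5. All the variables are already collected.
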